### Procedures

The program will be delivered by adult literacy teachers -with support from community health workers in the health literacy arm to assist with health-related content. All (health literacy and standard LLN) teachers will be trained in study procedures by University of Sydney researchers, and supplied with a study manual outlining rationale, procedures and timelines. Baseline measures will be taken on entry into the program and the short-term follow-up assessment will be conducted on completion of the program. Assessments will be split over several teaching sessions to spread student workload and delivered face-to-face by the adult literacy teacher (see Fig. 1). Participants will be invited to a further data-collection session 6 months following course completion, where they will receive $20 for their time. Students who are unable to attend the session will be able to complete the questionnaire by phone or mail.

### Blinding

Students will be invited to participate in a research trial but will be blinded as far as possible to its aims. Students will be informed simply that the study is about a new adult literacy program, the “Living Literacy Program”, but will not be informed that its purpose is to evaluate a health literacy program. Detail about the purpose of the trial will be given in a debrief statement following the final data collection session (6 months after course conclusion).

### Measures

Outcomes will be evaluated among students and teachers using a mixed methods approach. Table 2 summarises all outcome measures and timing of data collection for the study.

**Table 2 Tab2:** Data assessment schedule

	Baseline	Post intervention			
		Immed	2 months	6 months	6–12 months
Quantitative evaluation					
Demographics	X			X	
Health literacy measures • Single Item Literacy Screener (SILS) • Reading ability • Newest Vital Sign (NVS)	X				
Health skills	X	X			
Confidence (in health activities)	X	X		X	
Health Literacy Questionnaire	X	X		X	
Patient Activation Measure		X			
Shared Decision Making		X		X	
Student evaluation		X			
Healthy lifestyle (self-report) • Fruit and vegetable intake • Physical activity				X	
Health knowledge				X	
Qualitative evaluation					
Teacher interview - intervention			X		
Teacher interview - standard LLN			X		
Student interview - intervention			X		
Student interview - standard LLN			X		
Comm. health worker interview			X		
Education outcomes					
LLN outcomes		X			
Attendance at classes		X			
Enrolment in future TAFE classes					X

### I. Evaluation among students

#### Quantitative evaluation

##### Baseline measures

Include demographic and health literacy screening questions. Demographic information includes age, sex, country of birth, language spoken at home, and self-reported health status.

Health literacy includes: the Single Item Literacy Screener (SILS) “How often do you need to have someone help you when you read instructions, pamphlets, or other written material from your doctor or pharmacy?” [43]; self-report of reading ability “How would you rate your ability to read” [44], using a cut off of 3 “sometimes”/”okay” to denote poor literacy; Newest Vital Sign (NVS) [45] with minor modification to the food units presented in the stimulus to make it suitable for use in Australia.

We will take baseline measures of the main primary and secondary outcomes: functional health literacy skills (described below and in Additional file 1), confidence, and components of the Health Literacy Questionnaire (HLQ), described below.

##### Immediate post intervention outcomes

The primary outcome of functional health literacy skill will be assessed using a purpose designed measure informed by the intervention course core content (see Additional file 1):How to use a thermometer (score range 0–3).Interpretation of a medicine labels, (score range 0–5).Interpretation of a food label, 9 items (score range 0–10; not assessed at baseline).

Knowledge scores will be calculated using a marking scheme developed a priori (see Additional file 2). Health skills tasks will be assessed separately, as well as a combined outcome, which will be a weighted sum of the components.

Secondary outcomes will be:Confidence in health skills −10 confidence items modified from [46], measured on a 5-point scale ranging from “extremely” to “not at all” confident.1. Telling the doctor what is wrong; 2. Understanding your doctor; 3. Reading and understanding medicine labels; 4. Filling out medical forms by yourself; 5. Preventing problems with your health; 6. Taking care of your family and friends’ health; 7. Reading and understanding food labels; 8. Planning healthy meals; 9. Using a thermometer; 10. Asking the doctor questions.The Health Literacy Questionnaire (HLQ) [47] comprises 9 independent subscales to assess different aspects of health literacy. We selected 5 scales relevant to the learning objectives of the study intervention program (Having sufficient information to manage my health; Actively managing my health; Ability to engage with healthcare providers; Navigating the healthcare system; Understanding health information well enough to know what to do) rated on a 4-point scale or 5-point scale (25 items total).The 13-item generic Patient Activation Measure [48] includes self-reported ability of the individual to enact skills of health literacy using items assessing patients’ skills and confidence in managing their health.Student satisfaction with the health literacy program. As in [41] we will ask students to rate their course experience using 5-point Likert scale items: 1. overall rating (Excellent-Very poor); 2. if the course was (a) easy to understand, (b) helped them to understand their health (strongly agree-strongly disagree); 3. if they would recommend the course to family and friends (yes, definitely-definitely not).Shared Decision Making. A purpose-developed 14-item curriculum-based Shared Decision Making knowledge questionnaire (see Additional file 3) will cover Shared Decision Making competencies including comprehension of Shared Decision Making terms and concepts, probabilities and risk information. To assess the question asking component of the Shared Decision Making module we will ask all students to list (free-response) questions they considered important to discuss with their doctor, and code responses using content analysis. We will ask students who received the intervention to recall the AskShareKnow questions (free response), and analyse data following the method used by Shepherd et al. [37].

Six-month follow-up measures:

As assessed at baseline and immediately post interventionConfidence.Health Literacy Questionnaire.Shared Decision Making.decisional conflict using the SURE scale [49].decision making preferences using the Control Preferences scale [50].recall of the three AskShareKnow questions, use in health-care consultations based on self-report by participants, and comments on AskShareKnow materials (intervention only).

Additional measures4.Health knowledge using a 12-item curriculum based measure to assess retention of core components of health knowledge. 7 items related to health information and services, and 5 items were about serve sizes. See Additional file 4.5.Healthy lifestyle using self-report questions of daily: fruit and vegetable intake (number of serves); walking, and moderate and hard physical activity. These measures were taken from the 45 and Up Study [51].

6–12 month follow-upProgram retention rate: data on the proportion of adults enrolled in the program who complete the entire program, and proportion of classes attended will be collected.Enrollment in further TAFE adult education programs 12 months following course completion.

These final two endpoints will be assessed by enrolment records collected routinely by TAFE.

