**Methods/design:**

This is a cluster randomised controlled trial with a qualitative component. Participants are 300 adults enrolled in basic language, literacy and numeracy programs at adult education colleges across New South Wales, Australia. Each adult education institute (regional administrative centre) contributes (at least) two classes matched for student demographics, which may be at the same or different campuses. Classes (clusters) are randomly allocated to receive either the health literacy intervention (an 18-week program with health knowledge and skills embedded in language, literacy, and numeracy training (LLN)), or the standard Language Literacy and Numeracy (LLN) program (usual LLN classes, specifically excluding health content).

The primary outcome is functional health literacy skills – knowing how to use a thermometer, and read and interpret food and medicine labels. The secondary outcomes are self-reported confidence, more advanced health literacy skills; shared decision making skills, patient activation, health knowledge and self-reported health behaviour. Data is collected at baseline, and immediately and 6 months post intervention. A sample of participating teachers, students, and community health workers will be interviewed in-depth about their experiences with the program to better understand implementation issues and to strengthen the potential for scaling up the program.

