### Study objectives

This is a cluster randomised controlled trial that aims to evaluate a best practice model to:Deliver improvements in health literacy, confidence in health skills, Shared Decision Making, and knowledge about health and healthy behaviour, through a health literacy education program.Demonstrate improved engagement in learning (through higher attendance at classes) and greater enrolment in further adult education classes.Assess feasibility for delivery in a variety of locations (metropolitan, regional, and remote).

The health literacy program will be compared to a standard adult language, literacy and numeracy (LLN) program which would be expected to achieve some improvements which extend to health literacy outcomes also. Therefore this trial will examine the added benefit the health literacy program brings to health literacy related outcomes.

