### Intervention: the health literacy program

Australian adult education and public health experts adapted the UK *Skilled for Health* program to an Australian context. The revised program embeds key LLN skills development at the Australian Core Skills Framework level 2 into materials containing health-related topics focused on public health priorities (as identified by NSW Health) using Functional Context Education (FCE) methods [39]. In this approach students learn specified LLN skills through engaging with health material guided by their teacher [40]. We added a Shared Decision-Making program centred around the AskShareKnow questions (as described in [35]) that teaches participants about participating in decision making about their health, using recommended questions to elicit information from healthcare professionals, and discussing how to understand their responses.

The program consists of two teaching manuals:“Being Healthy”, which covers health skills such as using a thermometer, understanding prescriptions, communicating with health professionals, and Shared Decision-Making; and“Staying Healthy”, which focuses on diet and exercise (healthy lifestyle).

The 16 Being Healthy and 14 Staying Healthy topics are listed in Table 1. Teachers will be given a suggested delivery plan, with advice that they may diverge from this, according to the interests and capabilities of their students. The main requirement for delivery is that classes cover all 10 “core” topics considered central to the health literacy learning objectives and linked to the quantitative assessments. For the remainder of lessons students and teachers can select topics of most interest and relevance to the class.

**Table 1 Tab1:** Course content

Being healthy Teacher manual 1	Staying healthy Teacher manual 2
1.1 Taking temperature^a^	2.1 Getting involved
1.2 Checking medicine labels^a^	2.2 Food groups
1.3 Prescriptions	2.3 Food labels^a^
1.4 Dosage and timing	2.4 Nutritional information^a^
1.5 Health workers	2.5 Food temperature safety
1.6 Telling your doctor what is wrong^a^	2.6 Food date safety
1.7 Talking to your doctor^a^	2.7 What is a serve?^a^
1.8 Answering your doctor’s questions^a^	2.8 Budgeting
1.9 Immunisation and health screening	2.9 Understanding a diet
1.10 Asking questions^a^	2.10 Drinking enough fluids
1.11 Shared decision-making^a^	2.11 Heart Rate and Pulse
1.12 Completing medical forms	2.12 Being Active
1.13 Emergency services	2.13 Watch First Aid demonstrations

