#### Statistical analysis

The primary analysis will be by intention to treat. We will compare outcomes between the intervention and standard LLN arms for the primary outcome using a regression analysis that will account for clustering using appropriate methods [52]. We will use linear, logistic or ordinal logistic regression analyses as appropriate.

We will also conduct secondary analyses that adjust for baseline scores on the measures (where available), and health literacy and numeracy (measured with NVS). We will conduct these analyses separately. We will also conduct the same set of analyses for the primary outcomes, but using the intervention as actually received.

The statistician will be blinded to the allocated group definitions (i.e., health literacy vs standard LLN) until completion of the statistical analysis.

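### Health behaviour is a stated outcome but is measured only at 6 months, so the planned baseline adjustment cannot be applied to it and precision is lost

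*Protocol article*

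**What the plan says.** All references are to the protocol article.

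- **Status of the outcome.** The Abstract (Methods/design) ends its secondary outcomes with "health knowledge and self-reported health behaviour". The first aim under Study objectives includes "knowledge about health and healthy behaviour, through a health literacy education program". That phrase could mean behaviour itself or only knowledge about it, but the abstract makes behaviour an outcome.
- **Timing.** Among the additional six-month measures is "Healthy lifestyle using self-report questions of daily: fruit and vegetable intake (number of serves); walking, and moderate and hard physical activity". In Table 2 (Measures), the row "Healthy lifestyle (self-report) • Fruit and vegetable intake • Physical activity" has one mark, in the 6-month column.
- **Baseline.** Under Baseline measures: "We will take baseline measures of the main primary and secondary outcomes: functional health literacy skills", followed by confidence and components of the Health Literacy Questionnaire. Behaviour is not listed.
- **Analysis.** Under Statistical analysis, secondary analyses will "adjust for baseline scores on the measures (where available", and will also adjust for health literacy and numeracy measured with the Newest Vital Sign.
- **Content.** Delivery requires that "classes cover all 10 “core” topics considered central to the health literacy learning objectives and linked to the quantitative assessments". The class chooses the rest. In Table 1 neither "2.12 Being Active" nor topic 2.11 (heart rate and pulse) carries the core marker.
- **Teacher forms.** Intervention teachers rate the resources on a form in the manual, meant to be filled in after each lesson (Evaluation among teachers and community health workers).

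**The concern.** Habitual diet and activity usually persist within a person, so an earlier measurement of the same items is normally one of the best covariates for a later one. The plan relies on this for skills, confidence and the Health Literacy Questionnaire, where it collects a baseline. It does not do so for behaviour, and no analysis plan can recover data that the schedule does not collect.

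Three things are lost: precision in the 6-month comparison, any description of how the arms stood on behaviour at entry, and any estimate of change within students.

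A related point concerns interpretation. A class can meet the delivery rule in full and teach no physical-activity topic, yet its students are assessed on walking and on moderate and hard activity. Without a record of which classes taught those topics, the activity result is harder to explain.

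A wording slip sits beside this. The lead-in to the six-month list describes its items as already assessed at baseline and immediately after the program. The list includes shared decision making, the SURE scale and the Control Preferences scale. Neither the Baseline measures section nor Table 2 gives any of these a baseline.

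**Working it through.** **1. The plan's own figure.** Inputs from Sample size: difference 0.5 SD, 90% power, two-sided 5%, intra-cluster correlation 0.05, class size 10, 15% loss.

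- Unclustered, normal approximation: 2 × (1.960 + 1.282)² / 0.5² = 84.1, so 85 per arm. The t-based solution is 85.03, so 86, as stated.
- Design effect: 1 + (10 − 1) × 0.05 = 1.45. 86 × 1.45 = 124.7, so 125, as stated.
- Loss: 125 / 0.85 = 147.1, so 148, which the plan rounds to 150 (15 classes of 10 per arm).

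The stated sample size reproduces. It concerns the primary outcome. The article gives no SD, intra-cluster correlation, target effect or power for behaviour.

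**2. Effective sample for behaviour.** Assumption: 0.05 and 15% also apply here.

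- Analysed per arm: 150 × 0.85 = 127.5, or 8.5 per class.
- Design effect: 1 + 7.5 × 0.05 = 1.375.
- Effective n per arm: 127.5 / 1.375 = 92.7.
- Standard error of the difference, in SD units: √(2 / 92.7) = 0.147.

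**3. Detectable effect and power.** Adjusting for a baseline that correlates r with the outcome multiplies the residual SD by √(1 − r²). The effect detectable with 80% power is (1.960 + 0.842) × 0.147 × √(1 − r²). The values of r are assumed.

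| Analysis | √(1 − r²) | Detectable effect (SD) | Power for 0.3 SD |
|---|---|---|---|
| No baseline | 1 | 0.41 | 53% |
| r = 0.3 | 0.954 | 0.39 | 57% |
| r = 0.5 | 0.866 | 0.36 | 66% |
| r = 0.7 | 0.714 | 0.29 | 82% |

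The detectable effect falls by about 5%, 13% and 29% for the three values of r. If loss at 6 months were 30% (105 per arm, 7 per class, design effect 1.30, effective n 80.8), the figures would be 0.44 SD without a baseline and 0.42 to 0.32 SD with one.

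These are normal approximations. They ignore any gain from pair matching and any penalty for having only 15 pairs. They also take the intra-cluster correlation as unchanged by adjustment.

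**4. Content.** The core markers in Table 1 are on 1.1, 1.2, 1.6, 1.7, 1.8, 1.10, 1.11, 2.3, 2.4 and 2.7, which makes exactly 10. Diet therefore has some core cover (2.3, 2.4, 2.7), and physical activity has none.

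**The case against.** The strongest reply is that nothing here is invalid. Classes are randomised, so a comparison at 6 months alone is unbiased, and a cluster-adjusted interval is correct for it. Under the same assumptions, power for the plan's 0.5 SD is about 93% even without a baseline (0.5 / 0.147 − 1.96 = 1.44), so the loss matters only for smaller effects. Behaviour sits under additional six-month measures, not in the listed secondary outcomes at the end of the program. A lean baseline is also defensible for students with low literacy. All of this stands. It limits the size of the point but does not remove it.

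A reader might infer more than the article supports in four ways.

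- **That a positive result could simply be an entry difference.** With 150 per arm, the chance difference in baseline behaviour has standard error √(2 × 1.45 / 150) = 0.139 SD, or about ±0.27 SD. That is ordinary sampling error, which the cluster-adjusted interval already covers. Only the fraction r of it would carry through to 6 months.
- **That losses cannot be examined or nothing can be adjusted for.** Baseline data include demographics, self-reported health status, literacy screeners, confidence and Health Literacy Questionnaire scales. Students lost and retained can be compared on these. Only baseline behaviour is missing.
- **That optional activity topics contradict the core rule.** The rule links the core topics to the assessments. It does not say that every assessed item has a core topic.
- **That a null result on activity could not be interpreted.** The program lets classes choose topics, and the intention-to-treat question is what that program achieves. The per-lesson forms and the interviews with all intervention teachers may show what was taught, although the forms are resource ratings with no stated use as a delivery record.

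**Conclusion.** The point holds as a modest, cheap improvement to a stated outcome. Behaviour is measured once, at 6 months, and the planned baseline adjustment cannot reach it. The comparison remains unbiased. The cost is precision (about 0.41 SD detectable, against 0.39 to 0.29 SD) and the absence of any view of entry behaviour or within-person change. These sizes rest on assumptions that the article does not supply: that 0.05 and 15% apply to behaviour, and a correlation of 0.3 to 0.7. At the low end of that range the gain is small.

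The optional status of topics 2.11 and 2.12 is a matter of interpretation, not an error, and does not justify changing the core list. The lead-in to the six-month list does conflict with the Baseline measures section and Table 2, but it is a minor slip with no bearing on the behaviour comparison.

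**What to change.** 1. Add the same fruit and vegetable and physical-activity items to the baseline questionnaire: one mark in the baseline column of Table 2 and one line under Baseline measures. Adjust the 6-month comparison for them. The cost is slightly more burden for low-literacy students, in assessments already spread over several sessions and already containing health questionnaires.
2. Use the per-lesson teacher forms to record which intervention classes taught topics 2.11 and 2.12. Report that beside the activity result, and describe the result as the effect of the flexible program. The cost is a tick on an existing form and some effort to see that the forms are returned. The core list stays as it is.
3. Reword the lead-in to the six-month list so that it does not cover shared decision making, the SURE scale or the Control Preferences scale. This costs nothing.

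### Fruit and vegetable intake at 6 months is counted in self-judged serves, a unit the trial teaches to the intervention arm only, so part of any reported difference may reflect counting rather than eating

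*Protocol article*

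**What the plan says.** The abstract of the Protocol article (Methods/design) lists self-reported health behaviour among the secondary outcomes. Under the six-month follow-up measures, the diet part of that outcome is "Healthy lifestyle using self-report questions of daily: fruit and vegetable intake (number of serves"). On the origin of the questions the article says "These measures were taken from the 45 and Up Study"; their wording is not reproduced.

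Table 1 (Intervention: the health literacy program) lists topic "2.7 What is a serve" and marks it as core. The text above the table says "The main requirement for delivery is that classes cover all 10 “core” topics".

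The abstract describes the comparison arm as "usual LLN classes, specifically excluding health content". The Study design section agrees: those classes work on the same skills in non-health contexts.

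The same six-month assessment includes a 12-item health knowledge measure based on the curriculum, of which "5 items were about serve sizes".

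Table 2 (Measures) marks healthy lifestyle once, at 6 months.

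**The concern.** The respondent, not the study team, decides what one serve is. One arm has been taught how to decide and the other, by design, has not. If the teaching works, it may change the unit in which intervention students count as well as, possibly, what they eat. The protocol treats understanding of this unit as something the program may change, because it tests that understanding at the same assessment. Success on the serve-size knowledge items could therefore blur the meaning of the intake comparison.

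At stake is the interpretation of one component of one secondary outcome. A difference in reported serves may be partly or wholly a reporting difference, and a true difference may be hidden. Readers could not correct for this, because the direction is unknown.

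**Working it through.** **1. Do the documents set up a difference between arms in training on the unit?**

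- Unit of the outcome: number of serves, by self-report (six-month follow-up measures).
- Intervention arm: Table 1 carries seven core marks under the first manual (1.1, 1.2, 1.6, 1.7, 1.8, 1.10, 1.11) and three under the second (2.3, 2.4, 2.7). 7 + 3 = 10, which matches the stated number of required core topics. Topic 2.7 is therefore compulsory.
- Comparison arm: health content excluded (abstract; Study design).
- Understanding of the unit is itself measured: 5 of 12 knowledge items at 6 months.

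The contrast in training is explicit. Whether it carries through to the intake answers depends on the item wording, which is not shown.

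**2. Does anything stated remove the problem?**

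- Intention to treat, methods for clustering and a statistician blinded to group (Statistical analysis) do not correct a unit that differs by arm.
- Keeping students unaware of the trial's aims (Blinding) does not affect how they size a serve.
- Adjustment for baseline scores applies only where a baseline exists. None is marked for intake, and one would not solve this (see objection).
- No objective intake measure is described.

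**3. How large could it be?**

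The documents give no figure for intake, so there is none to reproduce. The only figures used below from the plan are those in its sample size section, which do reproduce:

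- Two means, 0.5 SD, 90% power, two-sided 5%: 2 × (1.960 + 1.282)² / 0.5² = 84.1, or 85.03 with the t distribution, rounded up to the stated 86.
- Design effect: 1 + (10 − 1) × 0.05 = 1.45; 86 × 1.45 = 124.7, or 125.
- Dropout: 125 / 0.85 = 147.1, or 148, rounded to 150 per arm.

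Illustration A. Assumed: true intake of 3.0 standard serves a day in both arms, and a trained arm that counts correctly.
Reported serves = true serves / (standard serves per personal serve).

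| Untrained serve, in standard serves | Control arm reports | Spurious difference (intervention − control) |
|---|---|---|
| 0.75 | 3 / 0.75 = 4.0 | −1.0 |
| 1.25 | 3 / 1.25 = 2.4 | +0.6 |
| 1.5 | 3 / 1.5 = 2.0 | +1.0 |

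If teaching corrects only half of the sizing error, the trained arm's serve is 0.875, 1.125 or 1.25 standard serves. It then reports 3.43, 2.67 or 2.40, and the spurious differences fall to about −0.57, +0.27 and +0.40.

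Illustration B. How often would a pure reporting shift reach two-sided 5% significance with no true difference? Take 125 analysed per arm and a design effect of 1.45, both from the plan's primary-outcome calculation, and an assumed SD of 1.5 to 2.5 serves.

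- Effective number per arm = 125 / 1.45 = 86.2.
- SE = SD × √(2 / 86.2) = 0.152 × SD, which is 0.23 to 0.38.
- Rate = Φ(b/SE − 1.96) + Φ(−b/SE − 1.96), where b is the reporting shift.
- b = 0.25 serve: about 10% (SD 2.5) to 19% (SD 1.5).
- b = 0.5 serve: about 26% (SD 2.5) to 59% (SD 1.5).

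The intended rate is 5%. True intake, sizing ratios, shifts and SDs are all assumptions. The illustrations show that modest mis-sizing could matter, not that it occurs.

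**The case against.** The strongest objection is that the instrument cannot be seen. The bracketed mention of serves is a condensed description, and the source questionnaire may define a serve for every respondent. An article commonly leaves item wording and question order to the questionnaire, so their absence is not itself a fault. This stands, and it makes the point conditional. A printed definition would shrink the problem but might not end it: respondents are basic-literacy learners, some answer by phone or mail, and one arm has practised applying such a definition.

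Four stronger readings are tempting and are not supported:

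- *The arms do answer in different units, so the result cannot be read as diet.* The documents support only that they may. Control students can know what a serve is from elsewhere, individual errors can cancel, and trained students can forget. The five serve-size items also give some means of interpreting the intake result.
- *Changing behaviour is a stated objective.* The Study objectives section most naturally refers to knowledge about health and healthy behaviour. The firm anchor for behaviour is the list of secondary outcomes in the abstract.
- *A baseline intake measure would have revealed the shift.* A baseline would be answered in untrained units in both arms. It could not separate a later change in counting from a change in eating.
- *The bias is as large as the effect the trial is sized for.* With an assumed SD of 1.5, shifts of 0.6 to 1.0 serves are 0.4 to 0.67 SD. Every input to that is assumed, and the plan's 0.5 SD belongs to the functional health literacy score. No target effect is stated for intake.

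The documents also give no unit for the physical activity items, so the point does not extend to them.

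**Conclusion.** The point holds as a conditional one. The diet outcome is counted in a unit that one arm is required to be taught and the other arm is not, and the article describes nothing that makes the unit common to both. Unless the borrowed questions already define a serve for everyone, part of any between-arm difference in reported serves may be a reporting difference.

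Size and direction are unknown: the illustrative range of −1.0 to +1.0 serves a day rests wholly on assumed values. Only the fruit and vegetable component of a secondary outcome is touched. The primary outcome and the sample size are unaffected. The change is worth making because it is cheap and has to be made when the question is asked, since analysis cannot recover a common unit afterwards.

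**What to change.** 1. Check whether the borrowed intake questions define a serve. Whether or not they do, print or read out the same short definition in household units with those questions for every respondent in both arms, for example pieces of fruit, cups of cooked vegetables and cups of salad. Use words rather than a picture card, because the Procedures section allows completion by phone or mail as well as in session.
2. Place the intake questions before the serve-size knowledge items, so that those items do not prompt the intake answers. On a mailed form the printed order can be set but not enforced.
3. State that the intake comparison will be interpreted alongside the five serve-size items, and that a difference in reported serves may partly reflect a difference in sizing.

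Cost: one or two added sentences on the questionnaire and a fixed question order. If the source wording has to change, comparability with the source cohort is slightly reduced. Replacing the borrowed questions outright would cost more of that comparability and is not needed for this point.
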